### Analysis

The statistical analyses will be based on the intention-to-treat as randomized principle. Treatment effects will be tested with survival analysis for dichotomous variables, and one-sample t-tests and ANCOVAs for continuous variables with baseline as covariate and condition as between group factor. When no deviations from distributional assumptions are detected, parametric ANCOVAs will be used.

Using Cohen's formula, effect sizes will be calculated as X_1_-X_2_/SD_pooled_, were X_1 _represents the pre-treatment scores, X_2 _the post-treatment scores, and SD_pooled _represents the pooled standard deviations of the pre- and post-treatment scores.

All the tests will be two-tailed with a significance level of 5%. Analyses will be performed using the Statistical Package for Social Sciences, version 15.0 for Windows (survival analyses, within-group analyses, Chi-square tests).

In the RCT [1] a pre to post treatment effect size difference of d = 1.24 (Cohen's d) was found on the main patient outcome measure BPDSI on 18 months. In the present study, the same treatment will be less intensive and executed in non-academic practice, so that a lower effectiveness can be expected. We therefore tentatively estimate the pre-post difference as d = 1.0.

It will be concluded that extra crisis support is definitely helpful if at the patient level a medium effect difference is found between the conditions with and without extra phone support. A possible small difference in effect will, although indicating that the extra support is helpful, probably not convince clinicians to implement this extra availability in their regular practice.

For the economic evaluation, analysis will also be performed according to intention-to-treat principle. The uncertainty around the cost-effectiveness and cost-utility ratios will be analyzed using bootstrapping techniques. Results of these bootstraps will be presented in cost-effectiveness planes

(showing all bootstrapped cost-effectiveness combinations) and cost-effectiveness acceptability curves (CEACs) which represent the probability that the intervention is cost-effective, given a certain threshold for the costs per unit of effect gained.

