#### Randomization

To prevent regional influences and enhance implementation TTA has to be equally spread over the different sites. Therefore a stratified randomization procedure will be used. The stratification procedure will be performed by a study-independent person and will be concealed for participating therapists, patients and researchers. Stratified per center, 50% of the therapists will be randomly allocated to the condition with extra phone support and 50% of the therapists to the condition without extra phone support. Each therapist will treat two patients either with or without phone support dependent upon the randomization. After completing the baseline assessment and signing the informed consent form patients will be randomly assigned to one of therapists of the participating institutes in their regions.

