#### Frequency of sessions and treatment period

In the RCT [1] the treatment period was three years with sessions twice a week. In the implementation study there will be sessions twice a week in the first year, but sessions once a week in the second year. In the implementation study we decided to do the first evaluation after a treatment period of eighteen months. This was decided for several reasons: different treatments have shown positive results after 1-1,5 years of treatment [1,15,16,18], effectiveness already became apparent after one year [1] and most drop outs occurred during the first 1,5 years of therapy [1,15].

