## Sample size and Data Analysis

### Sample size

The BPDSI-IV power calculation is based on the aim of showing a difference at the patient level between the conditions with extra phone support of the therapist outside office hours versus the condition without such support. Because we do not know what the effect of the extra phone support is, it is decided to use a medium effect size of 0.5, according to Cohen [61], for the power calculation. With a minimum of 2 × 30 patients per condition, the power to demonstrate such a difference between the two conditions with two-tailed alpha of 0.05 is 84. Therefore a minimum of 60 patients is required and accordingly 30 therapists need to be recruited.

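### Phone support is randomised to therapists within centres, but the stated ANCOVA has neither a therapist nor a centre term

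*Protocol article*

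**What the plan says.** The Randomization section makes the therapist the allocated unit and centre the stratum: "Stratified per center, 50% of the therapists will be randomly allocated to the condition with extra phone support". It adds: "Each therapist will treat two patients either with or without phone support dependent upon the randomization". Patients are then randomly assigned to a therapist in their region, so a patient's condition is whatever that therapist was allocated. The Sample size section asks for at least 60 patients and hence 30 therapists, with the calculation made for individual patients and no design effect.

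The Analysis section claims intention-to-treat as randomised and tests treatment effects with survival analysis for dichotomous variables and, for continuous variables, one-sample t-tests and "ANCOVAs for continuous variables with baseline as covariate and condition as between group factor". It names no therapist, centre or time term. Table 1 schedules the primary outcome, the BPDSI-IV, at baseline and at 6, 12, 18 and 36 months.

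**The concern.** Condition never varies within a therapist. Anything that makes two patients of one therapist more alike than patients of different therapists (skill, alliance, how the therapist handles crises) therefore goes straight into the comparison of conditions. A patient-level ANCOVA does not see this and takes its residual degrees of freedom from patients. Randomising patients to therapists limits similarity due to selection, but not similarity due to the therapist. The article itself treats the therapist as important: it studies alliance as a mediator, rates competence against a cutoff, and the intervention is the therapist's own availability.

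Centre was made a stratum to keep regional influences out of the comparison, and supervision and peer supervision are given per site. Leaving a balanced stratum out of the model leaves its variance in the residual, which makes the standard error too large.

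At stake are the p-value and confidence interval for the second aim. The interval matters even if the result is null, because the Strengths and limitations section would read a failure to find a difference as showing that any difference is small.

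**Working it through.** **Inputs from the article.** Two-sided alpha 0.05; effect size 0.5 ("it is decided to use a medium effect size of 0.5"); 60 patients and 30 therapists, hence 30 patients and 15 therapists per condition; cluster size m = 2. The therapist ICC, the centre variance and the number of centres are not given, so the values below are assumptions.

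**The plan's own power figure.** The article says "the power to demonstrate such a difference between the two conditions with two-tailed alpha of 0.05 is 84", read as 84%. With d = 0.5 and 30 per condition, the non-centrality is 0.5 × √(30/2) = 1.94. Two-sided power is then 49% by the normal approximation and 48% by the t distribution. With 60 per condition it is 78% and 78%. So 84% does not reproduce under either reading of the sample size. That is a separate problem; it matters here only because about 48% is the starting point to which clustering is added.

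**Therapist clustering alone.** Design effect DE = 1 + (m − 1) × ICC = 1 + ICC. True type I error of the patient-level test = 2 × P(Z > 1.96/√DE). Cluster-adjusted power uses 30/DE patients per condition and 30 − 2 = 28 degrees of freedom.

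| Assumed ICC | DE | Naive SE too small by | Type I error, formula | Type I error, simulation | Adjusted power, d = 0.5 |
|---|---|---|---|---|---|
| 0.05 | 1.05 | 2.4% | 5.6% | 5.6% | 45% |
| 0.10 | 1.10 | 4.7% | 6.2% | 6.2% | 43% |
| 0.20 | 1.20 | 8.7% | 7.4% | 7.3% | 40% |

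The simulation used 100,000 runs with 15 therapists per condition, two patients each, and a two-sample t-test. In the same runs a t-test on therapist means kept its error at 4.9% to 5.0%.

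**Adding centre.** Write the therapist, centre and residual shares of variance as t, c and e, with t + c + e = 1. If conditions are balanced within centres, the centre effect cancels from the difference. Its true variance is then proportional to 2t + e = 1 + t − c, while the naive test works with about 1. The two omissions therefore pull in opposite directions. With t = 0.05, the ratio is 1 + 0.05 − 0.05 = 1.00 for c = 0.05 and 1 + 0.05 − 0.10 = 0.95 for c = 0.10. Simulation with five balanced centres agrees closely:

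| Therapist share | Centre share | Patient-level test | Therapist-mean test without centre |
|---|---|---|---|
| 0 | 0.05 | 4.5% | 4.1% |
| 0.05 | 0.05 | 5.2% | 4.3% |
| 0.05 | 0.10 | 4.7% | 3.5% |

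The last column shows why both terms are needed: allowing for therapist while still omitting centre makes the test conservative.

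**The case against.** The best case for the plan is that the two omissions roughly cancel. With two patients per therapist the design effect is only 1 + ICC, and modest centre variance brings the error rate back to about 5%. With equal clusters the point estimate is essentially unaffected, and the article ties its judgement that phone support is definitely helpful to finding a medium difference. All of this stands, and it limits the size of the concern. It does not rescue the model, because the cancellation depends on two unknown variances and the interval around the estimate still has to be right.

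Nor is this a matter the article leaves open. It names the covariate and the factor, and what it names does not fit the randomisation.

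Some stronger readings are tempting but not supported:
- **That the test is certainly too liberal.** The direction depends on the therapist and centre variances, and neither is given.
- **That the ANCOVA uses one visit and discards patients without an 18-month score.** This is a natural inference from its form and from the 18-month aims. But the article names no visit and no missing-data rule, and such rules are commonly left to a fuller document. Survival analysis can use the intermediate visits.
- **That the 27% dropout from schema therapy in the cited trial measures the loss of 18-month data here.** That figure is treatment dropout over three years. The remark that "most drop outs occurred during the first 1,5 years of therapy" reports earlier trials and is not a forecast for this one.
- **That the economic bootstrap resamples patients.** The text says only "The uncertainty around the cost-effectiveness and cost-utility ratios will be analyzed using bootstrapping techniques"; the resampling unit is not stated.

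One practical objection also stands. Centres need only two therapists each, so 30 therapists could mean up to 15 centres. Fixed centre effects would then leave 30 − 15 − 1 = 14 therapist-level degrees of freedom instead of 28.

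**Conclusion.** The stated analysis of the condition contrast does not match the randomised unit or the stratification, and the article should be corrected on this. If there is no centre effect and the therapist ICC is 0.05 to 0.20, the type I error is about 5.6% to 7.4% instead of 5%, and properly adjusted power is 45% to 40% against about 48% unclustered. If centre also explains 5% or 10% of the variance, with ICC 0.05, the error is about 5.2% or 4.7%. The net effect is therefore modest and its sign unknown. These figures rest on assumed variance shares, exactly two patients per therapist, balance within centres and, for the centre results, five centres. The mismatch itself rests on no assumption. The survival analysis is likewise described without any allowance for therapist.

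**What to change.** State that the condition contrast on the BPDSI-IV will be estimated from a model with baseline BPDSI-IV, condition and centre, and a random therapist intercept. Cluster-robust standard errors by therapist, with a small-sample correction, are an alternative. Base the degrees of freedom on therapists (for example Satterthwaite). If there are many small centres, fit centre as a random effect or group the small ones, under a rule set in advance. Allow for therapist clusters in the survival analysis in the same way.

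Preferably, fit this as one mixed model to the 6-, 12- and 18-month scores, with time, condition-by-time and a within-patient covariance, and name the 18-month contrast as the primary test. This settles which visit is primary and lets patients without an 18-month score still contribute through their earlier visits. That part is a gain in efficiency and clarity, not the repair of a stated error.

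The cost is a change of wording and some programming; no new data or patients are needed. The analysis will have somewhat fewer degrees of freedom, and the interval may be slightly wider, depending on the number of centres.

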### Strengths and limitations

Many methodological requirements for a high quality trial are met. Allocation is concealed through randomization by an external researcher. Recruitment of the patients will be done after the standard intake procedure at each site. As this study takes place within different general mental healthcare departments located in different parts of the Netherlands the results can, to a large extent, be generalized to the population of borderline patients seen in regular mental healthcare in the Netherlands. A limitation of the present study is that the assessments will be performed by research assistants who cannot remain blinded to the treatment condition of the included patients, as is always the case in trials studying the effects of psychotherapy. Nor are the patients blind to treatment condition. In this study, however, added to the main interview-based outcome measures, self-report questionnaires will be administered, that will not be influenced by the research assistants.

Another limitation is the power of this study. This implementation study is powered to demonstrate a medium or higher effect of TTA. The failure to detect any difference between conditions, does not mean that they are equivalent, only that differences, if any, will be small. A small difference however does not imply lack of clinical significance. But to detect a small effect with a significance level of .05 and a power of 80, a power analysis shows that a sample of more than 3100 patients is necessary, which is not feasible for a trial on long-lasting psychotherapy.

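### Conclusions on phone support are not tied to the 5% test or a confidence interval: at 30 patients per condition a null result does not show that differences are small, and a small observed difference does not show help

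*Protocol article*

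**What the plan says.** All references are to the protocol article.

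- **Sample size.** Because the effect of phone support is unknown, "it is decided to use a medium effect size of 0.5". The text says "With a minimum of 2 × 30 patients per condition", but then that "a minimum of 60 patients is required and accordingly 30 therapists need to be recruited". The total of 60 fixes the number at 30 per condition. The stated power is 84.
- **Analysis.** Continuous outcomes are compared by ANCOVA with baseline as covariate. "All the tests will be two-tailed with a significance level of 5" per cent. The section then says how the result will be read: "extra crisis support is definitely helpful if at the patient level a medium effect difference is found". A small difference will, "although indicating that the extra support is helpful, probably not convince clinicians" to adopt it.
- **Strengths and limitations.** Failure to detect a difference "does not mean that they are equivalent, only that differences, if any, will be small".

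The statements on how to read the result mention neither a p-value nor a confidence interval.

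**The concern.** The added value of therapist phone availability is the study's second aim, and the Background calls it an important barrier to implementing schema therapy. The article says in advance what three kinds of result will mean: a medium difference, a small difference and no detected difference. Each reading depends on the size of the observed difference, or on the lack of significance, and not on how precisely the difference is estimated.

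With 60 patients the estimate is imprecise. A null result could be reported as showing that any difference is small when a medium or larger benefit has not been excluded. A small observed difference well within chance could be reported as a sign of help. Either could mislead services deciding whether to require out-of-hours cover.

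**Working it through.** **Inputs.** From the article: n = 30 per condition, d = 0.5, two-sided alpha 0.05, ANCOVA on baseline. Assumed: baseline-outcome correlation r from 0 to 0.8, because the article gives none. Therapist clustering and dropout are ignored at first.

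**The plan's own figure.** Power for d = 0.5 with 30 per condition is 49% by the normal approximation and 48% by the noncentral t, not 84%. Sixty per condition gives 78%, and one-sided testing with 30 gives 61%. ANCOVA with 30 per condition reaches 84% only if r is about 0.76, which the article does not state.

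**Formulas** (SD units):
- SE = √(2/30) × √(1 − r²), with 58 df unadjusted and 57 df for ANCOVA; the critical t is 2.002 in both cases.
- Smallest significant d = 2.002 × SE.
- Largest upper 95% limit of a non-significant result = 2 × 2.002 × SE (an estimate just short of significance plus one half-width).
- Miss rate = 1 − power, from the noncentral t with noncentrality 0.5/SE.

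| | r = 0 (unadjusted) | r = 0.5 | r = 0.8 |
|---|---|---|---|
| SE | 0.258 | 0.224 | 0.155 |
| Smallest significant d | 0.517 | 0.448 | 0.310 |
| Largest upper limit if non-significant | 1.03 | 0.90 | 0.62 |
| True d = 0.5 missed | 52% | 41% | 11% |
| p at observed d = 0.2 | 0.44 | 0.37 | 0.20 |
| p at observed d = 0.5 | 0.058 | 0.029 | 0.002 |
| 95% CI at observed d = 0.5 | −0.02 to 1.02 | 0.05 to 0.95 | 0.19 to 0.81 |

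**Null result.** For every non-significant result to exclude 0.5, 1.034 × √(1 − r²) must be below 0.5, so r must exceed about 0.88. Taking the stated 84% power at face value does not help: the implied SE is 0.5/(1.96 + 0.994) = 0.169, and the largest upper limit is 3.92 × 0.169 = 0.66. These are the extreme cases. With an observed difference of exactly zero, the upper limit equals the half-width: 0.517, 0.448 or 0.310. So some null results exclude 0.5 and some do not, and only the interval shows which.

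**Small difference.** At an observed d of 0.2, p stays between 0.44 and 0.20 across the range. With no true effect, an observed d of at least 0.2 in favour of phone support arises about 22% of the time at r = 0 and 10% at r = 0.8.

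**Medium difference.** An observed 0.5 is just significant when 0.517 × √(1 − r²) = 0.5, that is, at r of about 0.25. With an assumed therapist intraclass correlation of 0.05 to 0.10, two patients per therapist and therapist-level degrees of freedom, that threshold rises to about 0.39 to 0.44.

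**The case against.** **The positive rule contradicts the 5% test.** A reader might infer this from p = 0.058 at an observed d of 0.5. The article does not support it. The inference needs a finding to mean a bare point estimate, although the article elsewhere speaks of demonstrating and detecting differences and sets all tests at 5%. It also needs an unadjusted comparison, when ANCOVA is planned. Even then the two disagree only for observed d between 0.50 and 0.52. What stands is that the rule does not say which meaning applies.

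**A null result could hide an effect of 1 SD.** The value 1.03 belongs to r = 0 and a result just short of significance. A useful covariate lowers it, so the range over r has to be shown. The limit stays above 0.5 throughout the assumed range.

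**Strengths and limitations is already cautious.** It is a limitations paragraph, not a formal go/no-go rule. It disclaims equivalence and adds that a small difference may still matter clinically. That caution is right and should stay. However, the same sentence goes on to state a bound on the difference, and the data need not support that bound.

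**The effect-size scale is wrong.** A reader might infer this because the only printed formula uses an SD that "represents the pooled standard deviations of the pre- and post-treatment scores". That formula fits the pre-post comparison with the earlier trial in the same section. The between-condition 0.5 is set separately under Sample size, and a condensed article may leave its formula to the full plan. I make no point of it.

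**Conclusion.** The point holds in three parts of unequal strength.

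1. **Null result: wrong as written.** For any assumed r up to 0.8, non-significance alone does not confine the difference to less than the plan's own medium value of 0.5. This remains so if the stated power is accepted.
2. **Small difference read as help: not supported.** An observed 0.2 is far from significant for every r considered.
3. **Medium difference read as definite help: ambiguous.** It is not in clear conflict with the 5% level. Under ANCOVA with r above about 0.25 (about 0.4 with the assumed clustering), an observed 0.5 supports a benefit above zero. It does not establish a benefit of medium size: even at r = 0.8 the interval starts at 0.19.

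The figures rest on 30 analysed patients per condition and on the assumed r. Clustering by therapist or loss of assessments would widen the intervals. For example, losing 27% (the earlier trial's schema therapy dropout, used here as an assumption) leaves about 22 per condition and an unadjusted interval of −0.11 to 1.11 at an observed 0.5. The outcome, test and design are not in question here, only what may be concluded from them.

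**What to change.** Base every conclusion on the baseline-adjusted 18-month between-condition difference in BPDSI-IV, with its 95% CI.

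- **Analysis.** Call phone support helpful only if the CI excludes 0 in its favour. Report the size of the benefit as an estimate with its CI, and drop the claim of a definite medium effect. Remove the reading of a small difference as help in itself.
- **Strengths and limitations.** Keep the statement that a null result does not mean equivalence. Replace the claim that any difference is small with the range of differences that the CI does not exclude. If that range reaches 0.5 SD, call the result inconclusive.

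The cost is a few sentences, with no change to design or data collection. The downside is that inconclusive becomes the usual reading of a null result at this sample size. Unadjusted, the half-width of 0.517 means that no CI can lie wholly within 0.5 SD. At r = 0.5 the observed d must lie within 0.5 − 0.448 = 0.052 of zero, and at r = 0.8 within 0.5 − 0.310 = 0.19.

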#### Ethical principles

The participation in the study is voluntary. Participants are informed that they can cancel their participation at any time without disclosing reasons for their cancellation and without negative consequences for their future care. Participants will sign an informed consent.

#### Vote of the ethics committee

The design and conduct of the study was approved by the Medical Ethics Committee for General Mental Healthcare (METIGG 5230).

## Discussion

This study protocol is presented here to offer researchers the opportunity to consider the methodological quality of this study with a critical view. Therapists can benefit by considering the information regarding the practical applications of the proposed protocol on borderline patients in secondary care. The number of studies on ST for BPD is small, while BPD affects a large group of patients in regular mental healthcare. Research into the effectiveness of ST when it is implemented in regular mental healthcare can make an important contribution to the improvement of care for BPD patients. Also research into the added value of phone support outside office hours provided by the therapist can make an important contribution to the application of ST.

